## 2. Methodology

### 2.1. Trial Design and Setting

A parallel-group, single-blinded, two-arm randomized controlled superiority trial compares the effectiveness of HRTP to TAU with a 1:1 allocation ratio. Quantitative and qualitative data will be used to examine the effect of HRTP on racial trauma, depression (primary outcomes), and functioning (secondary outcomes). The trial will take place in an urban city in the province of Ontario, Canada.

Conducting the study in Ottawa contributes to the generalizability of the findings due to the city’s demographic and cultural diversity. As Canada’s capital, Ottawa attracts individuals from across the country and around the globe, providing a considerable mix of racial, ethnic, and linguistic communities. Based on the 2021 Population Census, Black people represented the largest racialized group at 8.5%, while Arabs and South Asian people each represented 5.8% of the total population of the city (Statistics Canada, 2021). As of 2021, there are also some 46,500 Indigenous people living in the Ottawa area, making up 3.2% of the population (Statistics Canada, 2021). This diversity means that the study is more likely to capture a range of lived experiences, cultural contexts, immigration histories, and socioeconomic backgrounds, thereby strengthening the external validity of the findings. A broad and varied participant pool will help ensure results are applicable to other urban centres and potentially even to more rural or international settings that share similar multicultural characteristics.

This study will follow the ethical principles of the Canadian Code of Ethics for Psychologists (CPA, 2017) and the Ethical Conduct for Research Involving Humans (TCPS-2, 2014). Informed consent will be obtained from all participants. The pilot study has been approved by the Research Ethics Board (H-02-22-7613) of the University of Ottawa, ensuring the protection of participant privacy and confidentiality. Participants may withdraw from the study at any time without consequence.

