### 2.2. Sample Size, Randomization, and Allocation

A sample of 96 participants (48 per group) is needed for an 80% probability to identify a difference between the treatment and control group. The power analysis for the sample size estimation was based on the means, standard deviations, and clinical cut-off for the primary outcomes (RTS, TSDS; Williams et al., 2022c, 2023b). Drawing on previous research, we hypothesized a standard mean difference of between 0.36 and 0.52, between the treatment and control group, which translates to a 10–20% decrease in the primary outcomes (i.e., RTS, TSDS) for individuals at the endpoint of treatment. Given these effect estimates, with an alpha of 0.05, an 80% power, and a 20% attrition, we estimated a sample size of approximately 96 (48 per group) will be needed. This randomized controlled trial will use an ANOVA and t-test (alpha error level = 5%, two-sided) for independent samples.

This sample size will require tailored recruitment efforts, community partnerships, and culturally safe retention strategies throughout the trial. Given differential attrition rates for racialized communities, the research team will spend additional time at intake discussing barriers to participation, issues with attendance, and address any participant concerns. Additionally, the research team will offer flexible session meeting times (e.g., evenings and weekends), and telephone check-ins as needed. The research team shall also compensate participants for both their completed sessions and batteries of measures.

In terms of blinding, the trial research team will be unaware of the group allocation. This includes the principal investigator and project coordinator who are overseeing the trial implementation, research assistants who will support recruitment and data collection, and the statistician conducting the analysis. See Figure 1 for the participant flow diagram of the trial.

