### 2.4. Participant Retention Strategies

The research team will use a range of equitable and inclusive strategies to ensure participant retention and mitigate attrition throughout the study. Once participants have completed the intake process and are fully onboarded, they will be assigned to a treatment group and a therapist. Through the sessions, the research team, including the therapists, will work with participants to sustain their participation and address barriers to their participation as they emerge. Participants will receive reminders based on their contact preferences, as well as notifications on our platform, for information about their sessions, questionnaires to complete, and any updates from the therapist and research team. Weekly sessions will be scheduled collaboratively with participants with flexibility incorporated into the available hours, and with the scheduling and rescheduling of sessions as needed. This flexibility will ensure therapists can identify and address any relevant barriers to a participant’s involvement. If a participant misses two sessions without further follow-ups with the research team, they will be invited to reconsider a better time to join the project. Further, participants will be paid for each session and packet of measures completed. For instance, within a pilot study of the HRTP trial, participants received $5 for each session as well as $30 for each battery of measures completed (e.g., intake and week 4).

The approach and strategies of this study are specific to racialized communities recognizing the historical and contemporary barriers to research access and participation. Specifically, we recognize participants will need explicit information and engagement as many might not have prior experience of participating in a clinical treatment study. Additional effort and time will be taken to answer participant questions, explain the process of their participation, and flexibility will be built into the design to support their continued involvement. These methodological considerations are essential to working with racialized communities experiencing racial trauma and the design and implementation are deliberate to centre the concerns of these communities to ensure their equitable and inclusive participation.

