As a first step of the onboarding process, interested parties will be required to respond to a standard set of questions (see Williams et al., 2022a for the full complement of questions). Sample questions from this set include:Have you had at least a one-semester graduate course (or the equivalent) focused on multicultural counselling skills? How have you applied it in your professional work?Are you willing to address racial differences with clients early in therapy? Give an example of how you would approach this.How would you respond if your client said you were a racist? Given that this question may require more context, assume that the client says this because you are either White or not the same race as they are.

Responses to the aforementioned questions will be used to gauge therapist interest, strengths, and gaps in training as well as to evaluate clarity, understanding of racism, and how it occurs in different settings. The Project Coordinator, and at least one other HRTP supervisor, will also review each submission against a study-specific rubric and follow up as needed on unclear elements or perceived gaps in responses. For instance, therapists may be assigned additional readings or role-play activities when their initial answers are insufficient.

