In a second step, the therapists will be given mandatory material for review. Therapists with minimal clinical experience overall or in working with racialized clients will be required to read and reflect on two academic articles. Specifically, one article describing the character traits and behaviours of an anti-racist clinician (i.e., Williams et al., 2022a); and another describing the underlying mechanisms employed by the HRTP (i.e., Williams et al., 2023a). All HRTP therapists, regardless of experience level, must also watch three workshop videos recorded by the principal investigator, presenting each of the three phases of treatment in depth, with interactive case examples. To ensure therapists have thoroughly engaged with the material given, the therapists will prepare a short written or oral reflection on each article/video assigned. In so doing, the therapists will be asked to consider what they liked about the reading/video (and why), what they did NOT like about the reading/video (and why), and what impact the reading/video has on theory and practice. Again, the Project Coordinator and at least one other HRTP supervisor shall review the reflections, using another study-specific rubric, and provide commentary and guidance as needed.

Should the above two phases be completed smoothly and absent any issue, the therapists will be ready to be matched with a client. If the Project Coordinator and at least one other HRTP supervisor believe the individual requires extra support, a mock first session will be organized between the therapist and a peer. The Project Coordinator will provide feedback on the audio recording of said role play.

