### 2.9. Primary Outcomes

Three primary outcomes will be measured at five time points for the treatment group (weeks 0, 4, 8, 12, and 28) and twice for the TAU control group (weeks 0 and 12). See Table 1 for the participants’ assessment schedule. Of note, there will be a differential assessment schedule for TAU versus HRTP participants. That is, HRTP participants are assessed on three more occasions than those in the TAU group. Two of these additional assessment periods are included within the intervention arm’s active treatment phase (weeks 4 and 8) to better understand how each HRTP phase impacts healing/racial trauma symptom severity. Week 4 roughly translates to the participants transitioning to the Healing phase and week 8 the Empowerment phase. Further, those in the control arm have no need for a post-treatment follow-up as upon receiving TAU, they may be immediately enrolled within the treatment group to receive the HRTP.

The *Racial Trauma Scale* (RTS; Williams et al., 2022c) is a 30-item clinical measure which examines the severity of traumatic symptoms due to racism. More specifically, the RTS asks individuals to “think about all the times when you have heard about, seen, or experienced racial discrimination” and how much they have been bothered by resultant thoughts, behaviours, or symptoms on a 4-point scale (where 1 is “not at all” and 4 is “extremely”). Of note, within this study specifically, when completing the RTS, clients will be asked to rate symptoms as per their lived experience over the previous month/30 days. An RTS total score is calculated by summing all item ratings together. Moreover, subfactors of the RTS include “Lack of Safety”, “Negative Cognitions”, and “Difficulty Coping”. Higher RTS total and subfactor scores indicate greater symptom distress. In consideration of the RTS’s convergent validity, RTS responses were found to be highly correlated with several measures of trauma, including the *PTSD Checklist for the DSM-5* (PCL-5; r = 0.79) and the *General Ethnic Discrimination Scale* (r = 0.76). The RTS was developed for and tested with diverse ethnoracial populations. The RTS also has excellent reliability (α = 0.97; Williams et al., 2022c).

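### Only HRTP participants are assessed at weeks 4, 8 and 28, so the blinding claimed for data collectors and the statistician is not delivered, and the arms differ in measurement before week 12

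*Protocol article*

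**What the plan says.** Section 2.1 labels the study "A parallel-group, single-blinded, two-arm randomized controlled superiority trial". Section 2.2 explains the label: "the trial research team will be unaware of the group allocation". Besides the principal investigator and the project coordinator, the roles listed as blinded are "research assistants who will support recruitment and data collection, and the statistician conducting the analysis". Participants and therapists are not listed.

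Section 2.9 and Table 1 set different schedules by arm. HRTP completes the three primary scales at weeks 0, 4, 8, 12 and 28, and TAU at weeks 0 and 12. The article says so openly: "HRTP participants are assessed on three more occasions than those in the TAU group". Table 1 schedules no measures for TAU at weeks 4 and 8. By week 28 it shows TAU participants as having left the study or begun HRTP.

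Section 2.12 says HRTP efficacy will be examined during treatment as well as at weeks 12 and 28, so the week 4 and 8 scores enter the analysis data. It defines the intent-to-treat set by a pre-treatment score plus the latest score on hand, given at least one attended session.

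**The concern.** The article names roles as blinded and then fixes a schedule under which an assessment at certain weeks can come from one arm only. Masking the arm label does not help when the visit pattern carries the same information. A reader of the eventual report would credit the trial with blinded data collection and blinded analysis that it did not have.

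Two further consequences bear on the week-12 comparison itself. HRTP participants fill in the primary scales more often beforehand, so repeated measurement is confounded with treatment. The arms also differ in what can serve as a last score for someone who drops out.

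**Working it through.** **Inputs.** Schedules: section 2.9 and Table 1. (Section 2.12 speaks of four HRTP time points but lists five weeks; the five listed weeks are used here.) Group size 48 and attrition 20%: section 2.2. Rule for the latest score: section 2.12. The rate of missing packs is not given and is an assumption.

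**1. The article's own count.** {0, 4, 8, 12, 28} minus {0, 12} = {4, 8, 28}, and 5 − 2 = 3 extra HRTP occasions. This agrees with section 2.9.

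**2. What a record reveals.** TAU has no pack at weeks 4 and 8, so a record at either week identifies HRTP with certainty. If each pack is missing independently with probability m, the share of HRTP participants with at least one revealing record is 1 − m² by week 8 and 1 − m³ by week 28.

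| Assumed m | By week 8 | By week 28 |
|---|---|---|
| 20% | 1 − 0.04 = 96% | 1 − 0.008 = 99.2% |
| 40% | 1 − 0.16 = 84% | 1 − 0.064 = 93.6% |

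Even with heavy missingness, most of the HRTP arm is identifiable before the week-12 comparison.

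**3. Who sees it.** Research assistants supporting data collection see it if they issue, chase or receive packs. The statistician sees it in any file that holds the week 4 and 8 scores section 2.12 intends to examine. The identification numbers described in section 2.3 hide who the person is, not when the person was assessed.

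**4. Measurement exposure.** Up to and including week 12, HRTP has weeks 0, 4, 8 and 12 (4 assessments) and TAU has weeks 0 and 12 (2 assessments).

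**5. The rule for the latest score.** Someone who stops providing data between weeks 4 and 12 can contribute a week 4 or week 8 score in HRTP. In TAU the only score is week 0, so that person either has no post-baseline value or is counted as unchanged. At the planned attrition, 0.20 × 48 = 9.6, so up to about 10 participants per arm could be handled differently. If symptoms ease with time in both arms, HRTP dropouts carry some of that easing and TAU dropouts carry none, which favours HRTP. The documents give no figures from which to size this shift.

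**6. After matching weeks 4 and 8.** {0, 4, 8, 12, 28} minus {0, 4, 8, 12} = {28}. Nothing in the schedule up to week 12 then reveals the arm, and the rule for the latest score has the same candidate weeks in both arms.

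**The case against.** **Limited effect on the scores.** RTS, BDI-II and TSDS are self-report, so staff do not score them. The two interviews take place at intake, before randomization. Week 28 falls after the only between-arm comparison and cannot bias it. All of this stands. It limits the harm from unblinded staff but does not make the blinding statement true, and it does not touch the unequal exposure or the rule for the latest score.

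**Operations may already mask the schedule.** Section 2.4 mentions platform notifications about questionnaires, so packs may be delivered electronically, and an article may leave data flow to the full protocol. It would therefore be too strong to say that every staff contact reveals the arm. Yet section 2.2 still has research assistants supporting data collection, and electronic delivery does not remove the visit pattern from the analysis file.

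**The coordinator.** A reader might infer that the coordinator knows each participant's arm, because section 2.5 says "The Project Coordinator, and at least one other HRTP supervisor, will also review each submission" and again "the Project Coordinator and at least one other HRTP supervisor shall review the reflections". The word other suggests an HRTP supervisor role. But those tasks are therapist onboarding before any client is seen. They show which therapists deliver HRTP, not which participants receive it, and the coordinator is not named as leading case supervision. Knowledge of individual allocation is an inference. What stands is a wording conflict with section 2.2. Likewise, section 2.4 counts therapists as part of the research team ("Through the sessions, the research team, including the therapists, will work with participants to sustain their participation"), but the section 2.2 list of blinded roles does not include them, so this is loose terminology.

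**Payment.** A reader might take 5 against 2 paid packs as the size of the problem. Section 2.4 also provides session pay, and both arms have 12 sessions. At pilot rates, 12 × $5 = $60 per arm. Totals are $60 + 5 × $30 = $210 against $60 + 2 × $30 = $120, and to week 12 $60 + 4 × $30 = $180 against $120. The gap is modest and rests on pilot rates being kept.

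**The phase question.** Weeks 4 and 8 are there to describe how HRTP phases relate to symptoms, and section 2.12 makes no between-arm claim at those weeks. The lack of TAU data then is a limit on interpretation, not an error in the planned comparison.

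**Conclusion.** The point holds for the research assistants who support data collection and for the statistician: the article states their blinding, and its own assessment schedule does not deliver it. The size is three arm-revealing occasions, two of them before week 12; 4 against 2 assessments up to and including week 12; and up to about 10 of 48 participants per arm whose last score could come from different weeks by arm. This assumes that these roles see pack timing or the full set of data columns, and that attrition is near the planned 20%.

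The documents do not support saying that all blinding in the trial is impossible, that the coordinator is shown to know individual allocations, or that the week-12 result would be seriously biased by unblinded staff. That participants know their own therapy contradicts nothing, since the article does not claim they are blinded. The point should be corrected, but it does not invalidate the design.

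**What to change.** 1. Give TAU the same self-report packs at weeks 4 and 8. Cost: 48 × 2 = up to 96 packs, and 96 × $30 = about $2,880 if the pilot rate is kept, plus a small added burden on TAU participants. This equalises exposure up to week 12 and lets the rule for the latest score work alike in both arms.
2. Give the statistician masked arm codes and only time points common to both arms until the week-12 between-arm analysis is locked; release week 28 afterwards. Without step 1 the common file is weeks 0 and 12 only. The rule for the latest score could not then be applied blind, because a last score at week 4 or 8 discloses HRTP.
3. Restate in sections 2.1 and 2.2 who is blinded and until when, and treat those who handle week 28 packs as unblinded. Reconcile the coordinator's place in the list of blinded roles with the section 2.5 wording, and the use of research team in section 2.2 with that in section 2.4. This costs wording only.

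Sections 2.4 and 2.9 also differ on whether TAU participants are offered HRTP after a 4-month follow-up or straight after TAU, and should be reconciled. Either reading leaves weeks 4 and 8 revealing the arm.

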### 2.3. Participant Eligibility, Recruitment, and Intake

*Participants* will be eligible for inclusion as *clients* if they have clinically relevant racism-related traumatic stress as determined by the UnRESTS (see the “Intake Measures for Inclusion” for more details), are at least 18 years of age, identify as Black, Indigenous, or a person of colour in Canada (BIPOC), have written and oral proficiency in English or French, and have access to the internet for online sessions. The only exclusion criterion includes having severe current substance or alcohol use as identified via the Mini International Neuropsychiatric Interview. However, participants who partake in another psychotherapy treatment or intervention will be advised to notify their external therapists about their participation in the study.

Participants will be recruited through the research team’s vast existing network of research partners and community mental health agencies. For example, the authors will partner with an academic research centre dedicated to the study of the biopsychosocial determinants of health in racialized, and specifically, Black communities in Canada. The centre’s existing participant pool and broad health sector network, including hospitals, community health centres, and community and religious organizations, will be leveraged. Mental health clinics within the study’s catchment will also be made aware of the study and invited to refer clients, when appropriate. Moreover, as is advised, to help build relationships and awareness of racial trauma, the HRTP, and the study, select offers will be sent to relevant associations (e.g., Ottawa Academy of Psychology) to conduct free/reduced-cost workshops/presentations for local mental health professionals (M. Williams et al., 2013). Interested individuals from the general public may also refer themselves to the study. These recruitment strategies can introduce selection bias; however, this bias is a common limitation in similar psychotherapy treatment studies (e.g., Foa & Williams, 2010).

Moreover, the research team will use targeted emails, social media posts, local bus ads, and word of mouth to advertise the study, instructing interested individuals to reach out to a study-specific email address. Once interest is confirmed, an email response will be sent with detailed information about the study and a consent form for consideration. The said study-specific email address will also present a direct contact with whom prospective participants may communicate should they have any questions or concerns about the study. Those interested in moving forward will be invited to partake in a 3 h virtual intake session (See Table 1 for the participants’ assessment schedule). During this intake, a trained research assistant will (i) describe important elements of the study, including the participant’s role and responsibilities; (ii) collect the necessary information from the participant to start a “file” (e.g., date of birth, gender, occupation, ethnoracial identity, contact information, emergency contact); (iii) and administer two semi-structured diagnostic interviews (i.e., the Mini International Neuropsychiatric Interview as well as the University of Connecticut Racial/Ethnic Stress & Trauma Survey). A 15 min break will be provided at the halfway point of the intake session. Using this intake information, the research team will continually and iteratively assess the demographic characteristics of the enrolled participants, gender and otherwise, to ensure sample heterogeneity and the generalizability of the findings (e.g., age, ethnicity, immigrant status, and socioeconomic status). Participant personal information and identifiers will be stored in a data management system to ensure participant privacy protection and data security. Data used for analysis will only include unique identification numbers assigned to each participant at intake. The data will be published in aggregate form and no participant identifier will be included.

Following intake, the participants will be randomly assigned to one of two groups: the HRTP (intervention) group or the control group (TAU). The randomization will be conducted using a computer-generated randomization sequence with stratification by age, gender, and the baseline level of racial stress (via the Racial Trauma Scale; Williams et al., 2022b).

This trial will use a stratified randomization process to incorporate study covariates (i.e., age, gender, and racial stress levels) each with 2 categories for a total of 6 strata. While transgender and gender non-conforming people account for 0.3% of Canada’s population (Statistics Canada, 2022), the trial will oversample this population because of low attrition rates and the reality of gender minority populations being traditionally excluded in clinical research (Adams & Miller, 2022; Owen-Smith et al., 2016). We will evaluate and report any gender differences in response to treatment and outcomes through subgroup analysis to consider the intersectionality of minoritized individuals (e.g., Adams & Miller, 2022).

